#### Modes of assessment

Screening is conducted by telephone. Cognitive and physical assessments are conducted face-to-face at the University of Queensland. Cognitive assessments are conducted by SO. Each cognitive assessment session lasts for 90 minutes. Physical assessments are conducted by an exercise physiologist and last for 30 minutes. Physical assessments are conducted immediately after the cognitive assessments. Self-administered questionnaires are used to assess psychological wellbeing. These are provided after the cognitive assessment, with participants instructed to complete them at home and mail them back within seven days using a provided reply-paid envelope. Participant perceptions of the two training programs are collected using a feedback form included with the other self-report instruments. Only training participants complete this feedback form.

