### Measurements

The primary outcome measures are indicators of cognitive functioning, aerobic capacity and strength. Secondary outcome measures are anthropometric measurements, resting heart-rate, blood pressure, indicators of psychological well-being and participant perceptions. All measures are assessed at baseline, post-test, and 6-month follow-up, except for the qualitative feedback which is assessed only at post-test.

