##### Program feedback form

This includes specific questions inviting participants to appraise the *Fit Bodies, Fine Minds *program. Written responses are invited on issues such as positive and negative outcomes of participation in the program, barriers to and facilitators of participation, enjoyment of activities and setting, and suitability of duration and frequency of sessions.

The form also includes two questions with 5-point Likert-scale response options. The first question is *How enjoyable was Fit Bodies, Fine Minds? *The response options are *extremely enjoyable*, *very enjoyable*, *quite enjoyable*, *somewhat enjoyable*, and *not at all enjoyable*. The second question is *How did you feel about attending Fit Bodies, Fine Minds? *The response options are *I looked forward to it ALL of the time*, *I looked forward to it MOST of the time*, *I looked forward to it SOME of the time*, *I could take it or leave it*, and *I DID NOT look forward to it at all*.

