## Discussion

"Nothing could be of greater importance to the imperatives imposed by global aging" than research into the benefits of exercise for cognition, according to Bortz [74]. This randomized controlled trial is designed to examine the effects of exercise training and combined exercise *and *cognitive training on the cognitive and physical functioning of community-dwelling older adults. It is hypothesized that

(1) both training groups will show significant improvements on measures of cognitive and physical functioning, relative to the control group,

(2) the combined training group (exercise *and *cognitive training) will show greater cognitive improvements than the exercise-only training group,

(3) improvements in cognitive functioning will be associated with improvements in aerobic capacity,

(4) improvements in cognitive functioning will be associated with improvements in psychological well-being; and

(5) participants will report positive experiences and outcomes from the two training programs.

If the training programs detailed in this protocol provide cognitive and physical benefits and are acceptable to older adults, they may represent a viable approach to improving cognitive functioning and quality of life in older adults. It is hoped that the findings from this study will add to a rapidly growing body of evidence which suggests that these types of interventions may be important for older adults, especially in a society that is facing the economic and social ramifications of an aging population.

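### The only described route to the feedback form is the week-16 assessment pack, so training participants who leave and miss that visit are not heard (minor, secondary outcome)

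*Protocol article*

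**What the plan says.** Four parts of the protocol article fix how participants' views are collected.

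- **Modes of assessment.** Cognitive assessments are face-to-face at the university. Of the self-administered questionnaires it says: "These are provided after the cognitive assessment, with participants instructed to complete them at home and mail them back within seven days". A reply-paid envelope is supplied. It then says: "Participant perceptions of the two training programs are collected using a feedback form included with the other self-report instruments". The control arm is left out: "Only training participants complete this feedback form".
- **Measurements.** All measures are taken at three time points, "except for the qualitative feedback which is assessed only at post-test". Participant perceptions are listed as a secondary outcome.
- **Program feedback form.** Written answers are invited on good and bad outcomes, barriers and facilitators, enjoyment, and whether the length and frequency of sessions suited people. In addition, "The form also includes two questions with 5-point Likert-scale response options": one item on enjoyment and one on feelings about attending.
- **Analyses and Discussion.** The qualitative data are to be analysed for themes. Hypothesis 5 is that "participants will report positive experiences and outcomes from the two training programs". The Discussion makes acceptability to older adults one of the conditions for calling the programs a viable approach.

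**The concern.** Read together, these sections describe one way of getting the form: attend the cognitive assessment at week 16 and take the pack home. Someone allocated to training who leaves the study before then, and does not come to that visit, is not offered it.

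For most outcomes that would be ordinary missing data. Here it matters more, because the reason for leaving may be the very thing the form asks about. People who met barriers, disliked the sessions or found three a week too many are plausibly over-represented among those who left. Themes they would have raised cannot appear in a thematic analysis of the forms that were returned.

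At stake are the completeness of the list of barriers and weaknesses, and the fairness of any statement that the programs were well received. The primary comparisons of cognition, aerobic capacity and strength are not affected.

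**Working it through.** **Inputs from the Sample size section.** 29 per group are required, with a 10% attrition allowance, giving 33 per group.

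**Reproducing the plan's figure.** 29 / (1 − 0.10) = 32.2, rounded up to 33, as stated. The two training arms together are 2 × 33 = 66.

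**How many might go unheard.** 10% of 66 = 6.6, about 7, leaving 66 − 7 = 59 who can receive the form. This takes the whole allowance as people who left and missed the week-16 visit.

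**Bounds on the share with a positive view among all allocated.** Let p be the share positive among responders and d the fraction unheard.

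- Lower bound (all unheard are negative): p × (1 − d)
- Upper bound (all unheard are positive): p × (1 − d) + d

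In whole people, with p = 100%: lower 59/66 = 89%, upper 66/66 = 100%.

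In round percentages, for other values:

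| Unheard (d) | Source of d | Positive among responders (p) | Range among all allocated |
|---|---|---|---|
| 10% | planned attrition | 100% | 90% to 100% |
| 10% | planned attrition | 90% | 81% to 91% |
| 20% | assumed | 90% | 72% to 92% |
| 30% | assumed | 90% | 63% to 93% |

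The first row gives 90% where the whole-person count gives 89%, because 6.6 people were rounded to 7.

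At the plan's own attrition figure, the largest possible overstatement is therefore about 10 points. It grows to 27 points (90% to 63%) only if 30% go unheard, a figure that is not in the protocol. Forms handed out but never mailed back would add to d; the article gives no figure for that.

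The share positive is used here only to put a size on the selection. The article sets no such percentage as a criterion for hypothesis 5.

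**The case against.** **The selection is partly an inference.** The article does not say that people who stop training are left out of the week-16 assessment, and a condensed article may leave their follow-up to the full protocol. This stands as a limit on the point: it applies to those who leave and also miss the visit, not to everyone who stops exercising. What remains is that the article does fix the delivery route and the single time point, and that route does not reach people who are absent.

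**Acceptability does not rest on the form alone.** The Feasibility section treats feedback as an addition to adherence and compliance data, and attendance records and session diaries will show who stopped. That also stands. Those records show that someone left, though, and not why.

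**A stronger reading is tempting.** The enjoyment item has four grades of enjoyable and one negative option, with no neutral one. The attendance item has three favourable options, one neutral and one negative. A reader might infer that hypothesis 5 is close to self-confirming and that the scales must be replaced. The documents do not support this, for three reasons:

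- The written part of the form asks every respondent directly about negative outcomes and barriers.
- The only analysis stated for the feedback is thematic. Nowhere are the ratings split into positive and negative or counted towards hypothesis 5, so the share of favourable options is not a predicted result.
- A scale graded from none to extreme enjoyment is a legitimate format. Preferring a balanced one is a matter of taste, and the lopsidedness does little harm if the full distribution is shown.

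Aim 5 itself is neutral in direction. The tilt bears on hypothesis 5 and on how acceptability is later described.

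**Conclusion.** The point holds as a minor one on a secondary outcome. As described, the collection route selects the feedback towards people who stayed to week 16, and so tilts the evidence for hypothesis 5 and for acceptability in the favourable direction. At the planned attrition, unanimous approval among responders would be compatible with about 89% to 100% approval among all 66 allocated to training.

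That size assumes that the full 10% both leave and miss the visit, that everyone else returns the form, and, at the lower end, that every unheard person is negative. The true effect is probably smaller if people who stop training still attend at week 16, and larger if attrition or mail non-return exceeds the allowance. The documents settle neither. They do not show that hypothesis 5 is bound to be confirmed or that the rating scales are invalid.

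**What to change.** 1. Post the feedback form, with the reply-paid envelope already in use, to every participant allocated to training when they stop or at week 16, whichever comes first.
2. Report the number of forms returned out of all allocated to training.
3. Show the full response distribution of both rating items, not a collapsed share called positive.

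The cost is a few extra mailings and a line in the report. Treatment, primary outcomes and sample size are unchanged. The acceptability figure may come out less favourable. Some who leave will not reply, so the change reduces the selection without removing it; reporting against all allocated lets the reader see how much remains.

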### Measurements

The primary outcome measures are indicators of cognitive functioning, aerobic capacity and strength. Secondary outcome measures are anthropometric measurements, resting heart-rate, blood pressure, indicators of psychological well-being and participant perceptions. All measures are assessed at baseline, post-test, and 6-month follow-up, except for the qualitative feedback which is assessed only at post-test.

#### Screening

##### Demographics

Includes gender, age, education, occupation, nationality, marital status, and language.

##### Health information

Includes height, weight, current level of physical activity, hearing, vision, chronic diseases, illnesses, and injuries.

##### Telephone Interview of Cognitive Status (TICS-m)

This is a brief telephone-administered dementia screening measure, modified slightly from the original to be more suitable for telephone use [48,53]. Participants complete a series of short cognitive tasks, such as counting backwards, remembering a list of 10 words, and answering general knowledge questions. Performance on the original TICS has been shown to be highly correlated with performance on the Mini-Mental State Examination [48,54]. The TICS-m is sensitive and specific [53]. A score of less than 30 (out of a possible 50) on the TICS-m is the cut-off for cognitive impairment [53].

#### Primary outcome measures: Cognitive functioning

Three domains of cognitive functioning are assessed: memory, executive functioning, and speed.

##### California Verbal Learning Test (CVLT-II)

This assesses the ability to use semantic categories to aid recall (memory) [56]. Participants are presented with words from four semantic categories (e.g. fruit, tools, clothing, herbs), listed in random order. Participants must then recall these words in a number of conditions, including immediate free recall (in which participants are asked to recall as many words as they can, in any order), delayed free recall (approximately 20 minutes after the original presentation), and cued recall (in which participants are asked to recall as many words as they can which fit in each of the categories) [57]. CLVT has satisfactory test-retest reliability [57]. Norms are also available for the CVLT, which has been shown to be somewhat sensitive to the effects of aging and neuropsychological impairment [57]. Scores include the number of words correctly recalled, the number of intrusions, and the number of repetitions. To limit test-retest effects, the original form is used at baseline and 6-month follow-up, with the alternate form used at the post-test assessment (16 weeks).

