### Aim

The aims of the present study are to:

(1) examine the impact of an exercise training program for older adults on cognitive and physical functioning,

(2) compare the impact of exercise training and a combined program of cognitive *and *exercise training for older adults (which has an equal number of total training sessions per week) on cognitive and physical functioning,

(3) examine associations between changes in aerobic capacity (as a result of exercise) and changes in cognitive functioning;

(4) examine associations between changes in psychological wellbeing (as a result of exercise) and changes in cognitive functioning; and

(5) identify older adults' perceptions of exercise training and combined exercise and cognitive training.

An exercise training program and a cognitive training program have been developed by the first author (SO), and will be evaluated in a randomized controlled trial. The content of these programs is based on previously successful training programs, and current theories regarding the relationships between exercise training, cognitive training, and cognitive functioning.

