### Sample size

Ninety-nine participants will be recruited for the study. A sample size of 12 participants in each of the three groups would enable detection of a within-group difference, from baseline to post-test, of 1 item (SD = 1.1) on Digit Span and 184 milliseconds (SD = 198) on Choice Reaction Time. Twenty participants in each group would enable detection of a between-group difference, at post-test, of 2 items (SD = 2.2) on Digit Span. Twenty-nine participants in each group would enable detection of a between-group difference, at post-test, of 118.8 milliseconds (SD = 160) on Choice Reaction Time. These sample size calculations assume a two-tailed alpha level of 0.05 and a power of 80%. The effect sizes and standard deviations are based on results from previous studies of physical activity for cognitive functioning in older adults (e.g. [11,49]). To account for attrition over time, the required sample size (29) is increased by 10% to 33 participants per group.

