### Analyses

Analysis of variance techniques will be used to assess changes over time (baseline, post-test, follow-up), and differences between groups, on the measures of aerobic capacity and cognitive functioning. Mean scores and variability scores will be used in these analyses. Variability scores may provide a more sensitive indicator than mean scores, of changes in cognitive functioning in older adults [71]. Where appropriate age, education and gender will be included as covariates. The Reliable Change Index will be used to determine the percentage of participants who demonstrate a significant change in performance, relative to their individual baseline [72,73]. This approach may provide a more accurate picture of changes experienced by participants than simple group differences [72,73]. Regression techniques will be used to identify the influence of changes in aerobic capacity on cognitive functioning. Regressions techniques will also be used to identify the influence of changes in psychological wellbeing on cognitive functioning.

The qualitative data will be analysed to identify themes related to participant perceptions of the program.

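### CVLT-II form is fixed by visit, so any week-16 change read within an arm or within a person includes the difference between forms; the comparisons between arms are not affected

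*Protocol article*

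**What the plan says.** The Measurements section sets the status of the test: "The primary outcome measures are indicators of cognitive functioning, aerobic capacity and strength". The CVLT-II is listed among the cognitive measures, in the memory domain.

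Its own section fixes which form is given when: "the original form is used at baseline and 6-month follow-up, with the alternate form used at the post-test assessment (16 weeks"). The stated reason is to limit test-retest effects. On reliability it says only "CLVT has satisfactory test-retest reliability", without a coefficient. It says nothing about whether the two forms are equally difficult, and it describes no variation of form order between participants.

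The Analyses section names both kinds of comparison: "Analysis of variance techniques will be used to assess changes over time (baseline, post-test, follow-up), and differences between groups". It adds a Reliable Change Index to "determine the percentage of participants who demonstrate a significant change in performance, relative to their individual baseline".

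In the Discussion, hypothesis 1 concerns improvement relative to the control group. Hypothesis 2 compares the combined programme with exercise alone.

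**The concern.** If the alternate list is harder, scores fall at week 16 and recover at week 40 without any true change. If it is easier, the same pattern appears as a training gain that is later lost. Because everyone changes form at the same visit, no analysis of these data alone can tell a form difference from real change.

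Two planned results would carry the shift: the change over the three visits, and the percentage of participants classed as reliably changed from their own baseline. At stake is whether a property of the test form is reported as improvement or decline on a primary memory measure.

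**Working it through.** **1. Where a shift enters.** Let d be the mean difference, alternate form minus original.

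- Week 0 to 16: true change + general practice + d.
- Week 16 to 40: true change + practice and re-exposure to the original list − d.
- Week 0 to 40: true change + practice and re-exposure to the original list. The form is the same at both ends, so d drops out.
- Arm A change minus arm B change over any interval: d appears in both and cancels.
- Regression of cognitive change on change in fitness or well-being: a constant d moves the intercept and leaves the slope alone.

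**2. The plan's own figures.** No stated figure concerns the CVLT-II. The 29 per group used below comes from Choice Reaction Time and reproduces: 2 × (1.96 + 0.842)² × (160/118.8)² = 28.5, rounded up to 29. Allowing for 10% attrition, 29/0.9 = 32.2, rounded up to 33.

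**3. Assumptions.** The article gives neither d nor the retest correlation r. I take d from 0.05 to 0.3 SD, r from 0.7 to 0.9, equal SDs at both visits and no true change.

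**4. Within-arm test of week 0 to 16 change.** SD of change = √(2(1 − r)), which is 0.775, 0.632 and 0.447 SD for r = 0.7, 0.8 and 0.9. The noncentrality is d/(SD of change) × √n. Example with r = 0.8, d = 0.2, n = 29: 0.2/0.632 = 0.316, and 0.316 × √29 = 1.70. The noncentral t distribution on 28 degrees of freedom then gives 38% rejection.

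Chance of rejection at a nominal two-sided 5%, n = 29:

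| d (SD) | r = 0.7 | r = 0.8 | r = 0.9 |
|---|---|---|---|
| 0.05 | 6% | 7% | 9% |
| 0.1 | 10% | 13% | 21% |
| 0.2 | 27% | 38% | 64% |
| 0.3 | 52% | 69% | 94% |

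For the week 0 to 16 change pooled over the three arms, on the same basis of 3 × 29 = 87 people, the rates are 31%, 83% and 99% at r = 0.8 for d = 0.1, 0.2 and 0.3. At r = 0.7 they are 22%, 66% and 95%.

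**5. Reliable Change Index at ±1.96.** The share wrongly classed as changed in the direction of the shift is 1 − Φ(1.96 − d/√(2(1 − r))). From 2.5% with no shift it becomes 3.4-4.1% (d = 0.1), 4.4-6.5% (d = 0.2) and 5.8-9.9% (d = 0.3) over r = 0.7 to 0.9.

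**6. Between-arm comparison of change.** In simulation (20,000 runs, 29 per arm, the same shift of up to 0.5 SD in both arms) the type I error stayed between 4.6% and 5.2%.

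**The case against.** The strongest reply is that a fixed order of alternate forms with a concurrent control arm is a defensible design. No list is repeated at consecutive visits, which serves the stated purpose, and the repeat comes 40 weeks after baseline. The main hypotheses are comparisons between randomised arms, where the shift cancels. The documents do not show that the forms differ at all, and a difference of 0.05 SD would barely matter. Any practice or control-group correction to the Reliable Change Index could also sit in the cited sources or in an analysis plan that is not shown.

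Most of this stands, and it limits the point. It does not remove it, because the allocation of forms is a design decision stated in the article. A later analysis plan could restrict how the results are read, but it could not recover the form effect.

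A reader might infer more than the documents support:

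- *That the treatment comparison is biased.* It is not, for an additive shift. Bias would need a form effect that differs by arm, for example through the memory-strategy sessions, and nothing in the article shows one.
- *That all change over time contains a form difference.* Week 0 to week 40 does not.
- *That the trial was sized on within-arm CVLT-II change.* The Sample size section does say that 12 per group "would enable detection of a within-group difference, from baseline to post-test", but only for Digit Span and Choice Reaction Time.
- *That the aim to "examine associations between changes in aerobic capacity (as a result of exercise) and changes in cognitive functioning" is distorted.* A constant shift does not alter the slope.

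**Conclusion.** The point holds for CVLT-II results that involve week 16 and are read without the control arm: within-arm change, the overall time effect and the Reliable Change percentages. The week 0 to 40 change has a separate and smaller problem, re-exposure to the baseline list. Hypotheses 1 and 2 and the regression slopes are untouched under an additive shift.

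The size is conditional. Over the assumed 0.05 to 0.3 SD and r = 0.7 to 0.9, the within-arm error rate runs from close to nominal (6%) to very high (94%). The effect on individual classification is smaller. If the forms are equivalent, only re-exposure and general practice remain. This is a weakness of modest weight in one of several cognitive measures, and worth correcting because the correction is cheap.

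**What to change.** Counterbalance form order within each arm: half the participants take original-alternate-original and half alternate-original-alternate. In the CVLT-II model, include form as a visit-level factor, or form order by visit. A main effect of form order alone is not enough, because it does not represent which form was taken at each visit.

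Counterbalancing does not remove general practice, and it leaves the baseline list repeated at week 40. Testing may also have begun already. The plan should therefore state as well that CVLT-II change and Reliable Change percentages will be interpreted only against the control arm at the same visit, for example with an index that subtracts the control-arm mean change. They should not be reported as stand-alone improvement or decline within an arm.

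The cost is a scheduling rule, one or a few degrees of freedom and a sentence on interpretation. Both forms are already in use, so no extra tests or staff are needed, and the sample size is unchanged.
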